#### Incentive payment structure

The five participating VA Networks' contributions to the incentive fund totalled $250,000. Based on this amount, we then simulated study results using pilot data and estimated rates of improvement to determine the greatest per-outcome incentive that we could provide per physician. The results indicated a per-patient maximum amount of $18.20, one-half from use of guideline-recommended medications and one-half from either BP control or appropriate response to uncontrolled BP.

Table 3 describes the intervention components and estimated incentive payouts for the study arms. For the physician-level incentive arm, each physician's reward reflected the number of successful outcomes achieved among the 40 randomly chosen patients. The group incentive earnings were based on the aggregated performance of the physicians. We allowed participants at the six group sites to choose how to allocate the group earnings (*e.g*., divide earnings among themselves as personal income or use them to provide patient education materials or other supplies for the clinic). Each group chose to divide the earnings evenly amongst themselves. For the combined incentive arm, the physicians received a payment that included their individual performance earnings as well as their share of the group's aggregated performance reward. Non-physician participants received their share of the group's aggregated performance reward.

**Table 3 T3:** Intervention components and incentive payouts

	Intervention components			Participants				Total estimated* incentive over entire study period	
				
Study Arm	Audit/ feedback report	Individual physician incentive	Group incentive	Physicians	Non- physicians	Performance evaluated	Per outcome per patient incentive award	Individual Physician	Group†
Physician incentive	•	•		•		Physician	$9.10	$2681	N/A

Group incentive	•		•	•	•	Physician	$9.10	N/A	$17206

Physician and group incentives	•	•	•	•	•	Physician	$9.10	$2696	$18872

No incentives (control)	•			•		Physician	$9.10	N/A	N/A

*Estimates based on outcome rates from pilot study and projected improvement rates per period as follows: individual arm - 0.05 for process measures (guideline-recommendation medication and appropriate response) and 0.03 for blood pressure control; group arm - 0.02 for process measures and 0.01 for blood pressure control; combined arm - 0.06 for process measures and 0.04 for blood pressure control.

†For a group that includes seven physicians. Group incentive award determined by summing the incentive amounts earned by all seven physicians in the group.

### Data collection

We developed a data abstraction tool and electronically collected data on the physicians' patients from the VA Computerized Patient Records System (CPRS). Abstractors at the Houston coordinating center collected data on patient demographics, vital signs, diabetes mellitus, cardiovascular conditions, renal conditions, terminal illness, and other relevant co-morbidities, laboratory values and medications, including dosages, allergies, contraindications, and patient refusals for all study sites. Additionally, we collected lifestyle modifications recommended by the provider or other medical staff members and information on study outcomes addressed at follow-up visits within a given timeframe. We collected hemoglobin A1c (HbA1c) levels in patients with diabetes, low-density lipoprotein cholesterol (LDL-C) levels in patients with hyperlipidemia, and colorectal cancer screening procedures among eligible patients to assess unintended consequences, *i.e*., neglect of these conditions or missed screening opportunities, that may have resulted from the intervention's focus on hypertension care.

After a training session, chart abstractors were required to complete 20 practice charts with 95% agreement on key data elements with all other abstractors and the trainer. During each period of data collection, the abstraction manager spot-checked charts for accuracy in abstracting key variables, addressing problem areas with abstracters as necessary. At the end of each period of data collection, we randomly selected at least three charts from each site in order to evaluate abstracter agreement. Also, we blinded chart abstractors to the study's objectives and to study arm assignments to ensure impartiality in the data collection process.

### Interviews - team planning, pay-for-performance perspectives, and unintended consequences of incentives

After participants received their second incentive payments and audit and feedback reports, the study team, including an industrial/organizational psychologist, interviewed 17 physician participants and 11 non-physician participants across the study sites to collect data about the strategies that they used to improve hypertension care, including clinic planning and team interaction shared mental models. Twelve physician participants and four non-physicians also completed a similar interview after the fourth disbursement of incentive payments and audit and feedback reports. These distinct interviews were intended to provide insights on how care strategies and planning may have evolved over time, and the drivers behind any observed changes.

Following the posting of the participants' final audit and feedback reports in April 2010, we interviewed 28 physicians and 10 non-physician participants across the study sites to ascertain their perspectives on financial incentives, the intervention's impact on team dynamics and care delivery for hypertension and non-related conditions, and organizational changes that occurred at the study site during the intervention period. Focusing on similar concept domains, we also interviewed primary care personnel, 24 physicians and 25 non-physicians across the sites, who did not participate in the intervention and primary care leadership at the 12 sites.

### Washout period and post-washout period data collection

The four-month post-washout performance period began 12 months following the posting of the final audit and feedback report to the study's website. To evaluate the persistence of the intervention, we will subsequently collect the same data that were collected during the intervention. A timeline of the study's activities, from physician recruitment to post-washout data collection, is presented in Figure 4.

**Figure 4 F4:**
[figure not shown]
**Study timeline**.

### Data analysis

The unit of analysis will be the physician. We will perform a repeated measures longitudinal analysis using mixed models to evaluate the effect of the intervention. We will evaluate three different predictors for each outcome: each incentive arm versus the control arm; individual-level incentive arms versus arms with no individual incentives; and group-level incentive arms versus arms with no group incentives. Models will be developed independently for each outcome. First, using scientifically relevant covariates selected *a priori*, we will construct a maximal model for each outcome as described by Cheng *et al*. [22]. The maximal model provides the flexibility to evaluate both the covariance structure and the list of covariates for inclusion in the final model. The relationship between each continuous covariate and the outcome will be explored to assess the need for covariate transformations. We also will determine whether any site-to-site variation exists and include the facility (cluster) as a random effect as necessary. We then will perform backward elimination to delete variables of no value, arriving at our final model.

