We randomized at the cluster (facility) level. To ensure that facilities of the same type would not be concentrated in the same arm, we employed the following constraints: all non-teaching facilities could not be in the same arm; all non-ALLHAT sites could not be in the same study arm; no arm could have two sites from the same geographic location; and at least two sites per arm had to meet the criteria for geographic integration (Figure 1). Using SAS version 9.1.3 (SAS Institute Inc, Cary, NC), a data analyst on the study team who was not involved in the processes of site selection or subject recruitment assigned a uniform random number to each of the possible allocations and selected the allocation sequence with the highest random number. Table 1 lists the characteristics of the study sites.

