### Power and sample size

The anticipated effect sizes were based upon a systematic review of financial incentives in healthcare [9]. In that review, the range of increases in performance using physician-level incentives was 5.9% to 25.3%, most of which were for preventive services such as immunizations. Because this study assesses treatment of a chronic disease requiring multiple types of interventions (*i.e*., medications, counseling, monitoring, lifestyle modification), rather than a single immunization, the increase in performance is anticipated to be somewhat less than those trials at the high end of this range.

The sample size calculation must take into account several factors. First, this is a cluster design, randomized at the facility level. Second, there is a measurement error associated with estimating each physician's proportion, because we can only sample a finite number of patients per physician. Finally, there must be a correction for multiple comparisons because we are testing two effects and an interaction. The sample size computation uses the non-central t-distribution and is based on a SAS^® ^program from Donner and Klar [18]. An iterative solution is required because the number of degrees of freedom depends on the sample size. The variance in measurements is the sum of the variance between hospitals, the remaining variation between physicians and the error variance of the measurement. Estimates of the variance between hospitals and the variance between physicians were obtained from pilot data. The error variance of measurement of the physician's proportion was calculated from the binomial distribution. Using these data, we estimated values of the intraclass correlation of 0.39 for appropriate medication and 0.14 for BP control.

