We provide power calculations for the process and outcome measures. We calculated effect sizes for various values of the difference in percentage use of appropriate medication and BP control we could detect between the study arms with 80% power using a two-sided t-test with 95% significance. Greater increases in power result from increasing the number of clusters than by increasing the number of cases within clusters [18]. However, it is much more difficult and costly to recruit more hospitals. We chose to use three hospitals per study arm with five physicians per hospital and 40 patient charts per physician. We determined that we could detect a difference of 17 percentage points between the mean proportions of appropriate medications in the arms, for an effect size of 1.59. Similarly, for BP control, we determined we could detect a difference of 15 percentage points between the mean proportions in the study arms for an effect size of 1.30.

We adjusted the sample size to account for anticipated physician participant attrition. Using VA physician workforce planning data, we estimated 5.8% would leave VA employment during the study. We adjusted our initial sample size, five physicians per site, to seven per site to account for attrition using the formula proposed by Lachin [19], defined as 1/(1-R)^2 ^where R is the drop-out rate.

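### Facility, the randomised unit, enters the model only if site variation is judged to exist, so the arm tests can lose their allowance for clustering

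*Protocol article*

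**What the plan says.** The protocol article, under Study sites and constrained randomization, states: "We randomized at the cluster (facility) level". Under Power and sample size it treats clustering as something the calculation has to allow for, adds between-hospital variance to the total, and reports that "we estimated values of the intraclass correlation of 0.39 for appropriate medication and 0.14 for BP control". The planned layout is given there too: "We chose to use three hospitals per study arm with five physicians per hospital and 40 patient charts per physician".

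Under Data analysis the plan is a repeated-measures mixed model, with this unit: "The unit of analysis will be the physician". On the randomised unit it says: "We also will determine whether any site-to-site variation exists and include the facility (cluster) as a random effect as necessary". The next sentence reads: "We then will perform backward elimination to delete variables of no value, arriving at our final model". The article nowhere commits to keeping facility in the model, says how its necessity will be judged, or exempts it from the elimination step.

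**The concern.** The sample size and the analysis treat the same quantity differently. The first takes between-hospital variation as given and puts figures on it; the second makes its existence a question for the trial data. Facility belongs in the model because it was randomised, whatever a check on 12 units shows. Failing to find site variation with so few facilities is weak evidence that there is none.

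If the term is dropped while hospitals do differ, the standard error of an arm contrast comes from variation among physicians, although the contrast rests on three hospitals per arm. Chance differences between a few hospitals can then be read as an incentive effect. The sentence governs both outcomes and all the comparisons listed in that section. It is a rule the article states, not a detail left to a fuller document.

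**Working it through.** The article gives no type I error to reproduce. Its detectable effect sizes (1.59 and 1.30) are a separate matter: they are not inputs here, and the program settings behind them are not given.

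**Inputs.** 4 arms × 3 facilities; ICC ρ = 0.14 (BP control) and 0.39 (medication), from Power and sample size; m = 7 physicians per facility (83 enrolled in 12 hospitals, 83/12 = 6.9), with the planned m = 5 as a second case; two-sided 5%, from "80% power using a two-sided t-test with 95% significance".

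**Assumptions.** One normal score per physician with total variance 1; ρ is the share of that variance lying between facilities; equal numbers per site; no covariates; repeated periods not modelled.

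**Step 1: degrees of freedom.** Between facilities within arms: 12 − 4 = 8. Within facilities at m = 7: 12 × 6 = 72. Pooled: 80.

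**Step 2: design effect, 1 + (m − 1)ρ.** At m = 7: 1 + 6 × 0.14 = 1.84 and 1 + 6 × 0.39 = 3.34. At m = 5: 1.56 and 2.56.

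**Step 3: how often a 5% F test would find the site variation.** The ratio of expected mean squares is θ = [1 + (m − 1)ρ]/(1 − ρ). The 5% critical value of F(8, 72) is 2.07, so the chance of detection is P(F(8, 72) > 2.07/θ).

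- BP control: θ = 1.84/0.86 = 2.14; 2.07/2.14 = 0.97; chance 47%.
- Medication: θ = 3.34/0.61 = 5.48; 2.07/5.48 = 0.38; chance 93%.

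At m = 5 the chances are 33% and 84%. For BP control, at the plan's own ICC, such a test misses the clustering more often than it finds it.

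**Step 4: error if facility is left out, by hand.** The expected pooled mean square is [8(1 + 6ρ) + 72(1 − ρ)]/80. The true variance of the contrast exceeds the one used by (1 + 6ρ) divided by that quantity.

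- BP control: (14.72 + 61.92)/80 = 0.958; 1.84/0.958 = 1.92, square root 1.386; the critical value 1.99 acts like 1.99/1.386 = 1.44; error about 15%.
- Medication: (26.72 + 43.92)/80 = 0.883; 3.34/0.883 = 3.78, square root 1.945; 1.99/1.945 = 1.02; error about 31%.

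**Step 5: simulation under no effect** (100,000 to 200,000 trials per cell, arm versus control, m = 7). Where a row does not say otherwise, facility is tested on 8 df when kept.

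| Handling of facility | BP control (0.14) | Medication (0.39) |
|---|---|---|
| Always kept | 5% | 5% |
| Kept whenever estimated variance is positive | about 5% | about 5% |
| Kept if an assumed 20% test is significant | about 6% | about 5% |
| Kept if an assumed 5% test is significant | about 9% | about 6% |
| Always kept, but physician-level df | about 8% | about 8% |
| Omitted | about 16% | 31% |

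At m = 5, the assumed 5% test gives 8.7% and 7.1%, and omission gives 12% and 25%. The pooled contrasts (individual incentive yes or no, group incentive yes or no) behave almost identically at m = 7: 9.2% and 6.1% with the 5% test, 15.6% and 31.1% with omission. In trials where the 5% test misses the site variation, the error is about 16% for BP control and 36% for medication.

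**Step 6: lower ICC.** The ICCs come from pilot data, and adjustment could reduce them. At an assumed ICC of 0.05, omission gives 7.5% to 8.7% and the 5% test 6.6% to 7.4% (m = 5 to 7).

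**The case against.** The strongest reply is that the article names no test and no significance level. Checking whether any site variation exists could well mean keeping facility whenever its estimated variance is above zero. That rule keeps it in about 88% (BP control) and 99% (medication) of trials and holds the error near 5% when 8 df are used. This stands: a 5% pre-test is an assumption, not the plan's procedure. But an undefined rule leaves the choice until after the data are seen, and the wording permits the harmful versions as readily as the harmless one.

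Second, the calculation is cross-sectional and the plan is longitudinal. If the effect is tested as change from the baseline period, a constant facility intercept cancels from within-physician contrasts, and facility-by-time variation is what matters. The article gives no figure for that. This limits the precision of the percentages. It does not justify a conditional term, since further periods on the same physicians add no facilities.

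Some stronger readings are tempting but not supported:

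- A reader might infer from the physician as unit of analysis that clustering is ignored. A mixed model on physician data is valid if facility stays in and arm effects are judged against between-facility variation.
- A reader might infer that about 80 physician-level degrees of freedom are planned. The article states none; the 8% row shows only why the replacement sentence should settle them.
- A reader might take 31% as the expected error for medication. That needs outright omission, which the article does not propose; at an ICC of 0.39 even a 5% test usually keeps the term.

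**Conclusion.** The concern holds for the conditional inclusion of facility. The plan randomises 12 facilities and sizes the trial on clustering, then lets the data decide whether the model allows for it. Under the retention rules examined, with 8 df when the term is kept, type I error runs from about 5% to about 9% for BP control and from about 5% to 6% for medication. Outright omission, at about 16% and 31%, is the outer bound. The exposure is mainly for BP control, where the lower ICC makes a check most likely to miss the clustering.

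These figures rest on the pilot ICCs, on reading them as the between-facility share of variance in physician scores, on one score per physician, and on the assumed retention rules. The fault in the rule does not rest on them. It should be corrected, because it bears on the validity of every arm comparison.

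**What to change.** Replace the conditional sentence under Data analysis with:

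> Facility is included as a random effect in every model, whatever its estimated variance, and is exempt from backward elimination. Arm contrasts are tested with small-sample, between-facility degrees of freedom (8 in the unadjusted four-arm model), for example by Kenward-Roger or Satterthwaite.

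The physician can remain the unit of analysis. A permutation test over the allocations permitted by the randomisation constraints is an optional check; Table 1 yields 428 × 24 = 10,272 labelled allocations.

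The cost is one sentence and no new data. Confidence intervals become wider. Compared with leaving facility out, the half-width grows by roughly 1.386 × 2.306/1.990 = 1.6 for BP control and 1.945 × 2.306/1.990 = 2.3 for medication (m = 7; 2.306 and 1.990 are the two-sided 5% t values on 8 and 80 df). That extra width reflects the information three hospitals per arm actually provide.

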**Methods/design:**

This randomized controlled trial tests whether explicit financial incentives promote the translation of guideline-recommended care for hypertension into clinical practice and improve blood pressure (BP) control in the primary care setting. Using constrained randomization, we assigned 12 Veterans Affairs hospital outpatient clinics to four study arms: physician-level incentive; group-level incentive; combination of physician and group incentives; and no incentives (control). All participants at the hospital (cluster) were assigned to the same study arm. We enrolled 83 full-time primary care physicians and 42 non-physician personnel. The intervention consisted of an educational session about guideline-recommended care for hypertension, five audit and feedback reports, and five disbursements of incentive payments. Incentive payments rewarded participants for chart-documented use of guideline-recommended antihypertensive medications, BP control, and appropriate responses to uncontrolled BP during a prior four-month performance period over the 20-month intervention. To identify potential unintended consequences of the incentives, the study team interviewed study participants, as well as non-participant primary care personnel and leadership at study sites. Chart reviews included data collection on quality measures not related to hypertension. To evaluate the persistence of the effect of the incentives, the study design includes a washout period.

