### Study sites and constrained randomization

We partnered with five Veterans Affairs (VA) regional networks to implement the study. Within these networks, hospital-based VA outpatient clinics that could conduct human subjects' research and had eight or more eligible primary care physicians were potential study sites. Of the 22 potential study sites, only 12 met the requirements for study implementation: hospital director approval; Institutional Review Board (IRB) and VA Research and Development (R&D) approval; having a credentialed individual willing to serve as the site's PI; and having at least five consented physician participants at time of randomization. We stratified these 12 study sites on the following characteristics expected *a priori *to be associated with responses to financial incentives and the study outcomes of interest: teaching status, geographic location, participation in the ALLHAT study [4] (a very large trial of various medications used to treat hypertension in both VA and non-VA settings that included intensive education regarding hypertension control and use of evidence-based hypertension treatment at participating sites), and the degree of clinic geographic proximity within the primary care setting at each study site. We identified a hospital as a teaching facility if it was listed in the Association of American Medical College's (AAMC) Council of Teaching Hospitals (COTH) directory or if the American Medical Association's (AMA) Fellowship and Residency Electronic Interactive Database (FREIDA) listed the VA facility as having a 'major' affiliation with a medical school. To determine geographic region, we used US Census Bureau information to identify the corresponding Census Division for each site. Study site investigators provided clinic layout information, and we designated sites as being integrated if the layout was amenable to group cohesion (*e.g*., the primary care clinic offices were located on the same floor at the study site).

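### Backward elimination, run separately for each outcome with no protected terms, picks the final model in a 12-site trial and can drop the randomisation factors, including ALLHAT status, whose constraint read literally excludes no allocation

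*Protocol article*

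**What the plan says.** The Data analysis section starts each outcome from a maximal model. Its covariates are chosen in advance but not listed, and both the covariance structure and the covariate list stay open to revision. The section ends: "We then will perform backward elimination to delete variables of no value, arriving at our final model." No term is exempted and no retention criterion is given. The planned comparisons are each incentive arm against control, individual incentive against none, and group incentive against none.

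Under Study sites and constrained randomization, the article says "We stratified these 12 study sites on the following characteristics expected" in advance to bear on both the response to incentives and the outcomes. They are teaching status, location, ALLHAT participation and clinic proximity. The stated aim of the constraints is "To ensure that facilities of the same type would not be concentrated in the same arm". Three of them read "all non-teaching facilities could not be in the same arm", "all non-ALLHAT sites could not be in the same study arm" and "no arm could have two sites from the same geographic location". The fourth requires at least two geographically integrated sites in every arm.

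On size, the abstract says "we assigned 12 Veterans Affairs hospital outpatient clinics to four study arms", and Power and sample size says "We chose to use three hospitals per study arm with five physicians per hospital and 40 patient charts per physician".

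**The concern.** An adjustment set chosen by looking at the outcome, then tested as if it had been fixed, understates the uncertainty of the treatment effect. The understatement is worst where independent units are few. Here the incentive is assigned to sites, and there are 12. A site-level covariate that happens to track the site residuals tends to survive elimination and shrinks the error term. One that fails to do so is dropped, even if the trialists had good reason to expect it to matter.

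The same step can remove the factors that shaped the randomisation. This is most relevant for ALLHAT participation, because its constraint, as worded, did no work. Adjustment in the model is then the remaining direct safeguard. Selecting separately for each outcome also means that the medication and BP results may rest on different adjustment sets.

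**Working it through.** **Design size.** 4 arms × 3 hospitals = 12 sites, which matches the abstract. Between-site degrees of freedom after fitting arms: 12 − 4 = 8.

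**Site counts from Table 1.** Non-ALLHAT: 4 (Boston, Newington, Birmingham, Saginaw). Non-teaching: 2 (Newington, Saginaw). Integrated: 8. Census Divisions: 6.

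**Do the constraints bind?** Labelled allocations: 12!/(3!)^4 = 369,600, or 369,600/4! = 15,400 partitions into four triples. Each constraint taken alone excludes:

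| Constraint | Allocations excluded |
|---|---|
| Teaching | 67,200 |
| ALLHAT (literal wording) | 0 |
| Geography | 279,744 |
| Integration | 309,120 |

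The permitted set is 10,272 allocations (10,272/24 = 428 partitions), with or without the ALLHAT rule. Four sites cannot fit in an arm of three, so the rule cannot be broken.

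ALLHAT spread among permitted allocations, compared with unrestricted allocation:

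| Pattern of the 4 non-ALLHAT sites | Permitted | Unrestricted |
|---|---|---|
| Three in one arm | 40/428 = 9.3% | 4 × 280/15,400 = 7.3% |
| 3:1 across the individual-incentive contrast | 5,280/10,272 = 51.4% | 448/924 = 48.5% |
| 4:0 across that contrast | 528/10,272 = 5.1% | 56/924 = 6.1% |

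In the unrestricted column, 924 = C(12,6), 448 = 2 × C(4,3) × C(8,3) and 56 = 2 × C(8,2). The constraint set leaves ALLHAT about as it would fall by chance.

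**What does the selection step do to the test?** Null simulations on 12 site means, with allocations drawn from the permitted set, arm terms always kept and no true incentive effect. Candidates were eliminated by p-value at thresholds of 0.05 to 0.20, which are assumed because the article gives none. The incentive term was then tested at two-sided 0.05 in the final model.

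| Candidates | Test | All kept | After elimination |
|---|---|---|---|
| Teaching, ALLHAT | arm v control | 4.3–5.5% | 6.6–8.2% |
| Teaching, ALLHAT, integration | individual incentive | 4.5–5.6% | 7.4%, 8.6%, 9.4% (thresholds 0.05, 0.10, 0.20) |
| Teaching, ALLHAT, 2 invented site covariates | arm v control | 4.3–5.5% | 9.6–12.9% |
| Teaching, ALLHAT, 4 invented site covariates | arm v control | 4.3–5.5% | 17.4–23.5% |
| 6 null physician-level covariates (7 physicians per site, ICC 0.14 and 0.39) | arm v control, 8 df | not run; with no candidates 4.7–5.5% | 5.1–5.4% |

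The 4.3–5.5% range covers all three arm v control rows with site-level candidates together. Each cell used 3,000 to 8,000 runs where the count was recorded. At 6,000 runs the Monte Carlo standard error near 5% is √(0.05 × 0.95/6,000) = 0.28 percentage points. Adjustment alone holds the level; elimination raises it.

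**Would ALLHAT survive?** With three candidates and threshold 0.05, ALLHAT was dropped in 93% of runs with no true ALLHAT effect, 77% with an effect of one between-site SD and 39% with two.

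**Can everything be kept?** No. Arms, teaching, ALLHAT and integration use 7 of 12 degrees of freedom. Adding the six Census Divisions brought the rank to 12 in 2,290 of 3,000 sampled allocations and to 10 or 11 in the rest, leaving 0 to 2.

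**The case against.** - **Unstated inputs.** The article lists no covariates, gives no threshold and cites a published modelling method that is not at hand. The candidate list is fixed in advance, and the randomisation factors may not be in it. The unit of analysis is the physician, and the provider characteristics in Table 2 are physician-level; with such candidates only, the inflation all but vanishes. This stands. A reader might infer a type I error of 10–24%, but those figures need two to four site covariates that the article does not mention.
- **Simplified model.** The plan is a repeated-measures mixed model, and the first performance period precedes the incentives. If the effect is read as an arm-by-time contrast, stable site differences such as ALLHAT status largely cancel. This stands too: the simulations show direction and rough size only.
- **Condensed article.** Forced terms and retention criteria may sit in a fuller document. Their absence is therefore no fault. The elimination step, however, is a stated rule for reaching the final model.
- **ALLHAT.** A reader might infer that ALLHAT was unbalanced by design, or is unbalanced in this trial. Neither follows. It was left to chance and the other constraints, and the realised allocation (Figure 1) is not shown. The rule may also have meant that no arm could be wholly non-ALLHAT. On that reading it binds, removing exactly the 40 partitions above.

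**Conclusion.** The concern holds in limited form. The article makes data-driven elimination, per outcome and without protected terms, the route to the model in which the incentive effect is judged. Nothing keeps the factors that the article itself expected to be associated with the outcomes.

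If site-level covariates are candidates, the test is anti-conservative: about 7–8% at nominal 5% with teaching and ALLHAT, assuming elimination by p-value and a site-mean analysis. It is higher with more site-level candidates, negligible with physician-level candidates only, and probably lower for an arm-by-time contrast.

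That the ALLHAT constraint excludes nothing is exact arithmetic on its literal wording. It is a reason to protect ALLHAT in the model, not evidence that this trial's arms differ on it. The point is worth acting on because the change is cheap; it does not undermine the design.

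**What to change.** 1. Remove backward elimination from the primary analysis.
2. Before any model by arm is fitted, name one short adjustment set for all outcomes, kept regardless of significance: period-1 performance (as the baseline occasion in the longitudinal model or as a covariate), ALLHAT status and teaching status.
3. Report any selected or wider model as a sensitivity analysis.
4. Tabulate ALLHAT status by arm, and state what the ALLHAT constraint was meant to exclude.
5. State openly that geography cannot be fully adjusted for with 12 sites. Integration is balanced already: 8 integrated sites with at least two per arm forces exactly two in each. A term for it is not needed to remove confounding, although leaving it out keeps any integration effect in the error term.

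**Cost.** A wording change and two site-level degrees of freedom: 8 to 6, critical t 2.31 to 2.45, so intervals about 6% wider (2.45/2.31) before any gain from explained variance. If period-1 performance also enters as a site-level term, three are used: 5 left, critical t 2.57, about 11% wider (2.57/2.31). No new data are needed.
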